## Abstract

**Background:**

Psychotic disorders such as schizophrenia present a significant challenge to health care systems due to their high disability rates and treatment costs. With discontinuation rates for antipsychotics reaching over 40% in the first year and 80% after 3 years, it is crucial to tailor antipsychotic selection and dosing early in treatment. Personalized precision psychiatry, underpinned by pharmacogenetics, holds considerable potential in individualizing antipsychotic treatment for patients with first-episode psychosis. An internationally pioneering method called 5-step precision medicine (5SPM) focuses on the application of pharmacogenetics to clinical practice. The recently launched Prevention and Early Intervention in Mental Health (PRINT) program in Salamanca, Spain, integrates this method to enhance early intervention for adolescents and young people with first-episode psychosis.

**Objective:**

The Clinical Utility of Early Intervention Including the 5SPM Method in First-Episode Psychosis (CLUMP) project aims to explore whether an early intervention model of personalized precision psychiatry including pharmacogenetics improves adherence to antipsychotic medicines and, therefore, clinical and functional outcomes in young people experiencing the first episode of a psychotic illness.

**Methods:**

To achieve our objectives, we shall compare adherence to the first prescribed antipsychotic medication and clinical and functional outcomes between patients with first-episode psychosis. We shall compare 2 cohorts: cohort 1 will receive the recently introduced PRINT program including the 5SPM method, and cohort 2 will have received standard care provided by mental health services before the PRINT program implementation. The primary outcome to measure treatment adherence will be all-cause discontinuation proportions during the 1-year follow-up. Secondary outcome measures will include pragmatic efficacy, tolerability, and functional outcome measures. For additional comparative purposes, we shall analyze the environmental, clinical, and pharmacogenetic information of patients with psychotic disorders of more than 5 years of evolution and with other mental disorders whose data are currently stored and have been ethically approved for research use. A total of 300 patients will be included in the study. Analyses will include descriptive statistics, comparison tests, Kaplan-Meier survival curves, multivariate log rank tests, qualitative analysis, and cost-benefit evaluation.

**Results:**

Ethics approval was obtained in June 2023. Recruitment for the CLUMP project began in January 2025, and enrollment for cohort 1 will continue until May 2026. All data collection is expected to be completed by June 2027. Data analyses are estimated to take approximately 6 months. The project is scheduled to conclude in December 2027.

**Conclusions:**

The CLUMP project is set to provide the first clear blueprint for implementing and evaluating the impact of personalized precision psychiatry based on pharmacogenetics in the context of early intervention programs for the benefit of young people experiencing the first episode of a severe mental illness such as schizophrenia.

**International Registered Report Identifier (IRRID):**

DERR1-10.2196/74408

## Introduction

### Background

Psychotic illnesses such as schizophrenia and related conditions are a major issue for public health care systems; they cause severe disability and are expensive to treat. As the illness becomes manifest during adolescence or young adulthood, nonspecific signs such as anxiety, depression, and emerging psychotic features form a prelude to the full psychotic syndrome that may last for months or even years before patients seek help or receive treatment. This duration of untreated psychosis is inversely related to outcome. Therefore, providing effective treatments as soon as possible, shortening the duration of untreated psychosis, may prevent the development of a more severe illness, improve quality of life, and lead to recovery in many cases [1,2]. Many people at an early stage of their psychotic illness, in addition to delusions or hallucinations, may develop cognitive problems that underpin disability. These impairments contribute to problems in functional outcomes that are considered by patients and their relatives to be as important as the phenomena that professionals focus on. Furthermore, the evolution of psychotic disorders varies hugely and raises the question of why certain people improve and others stay unwell despite having gone through similar interventions [1].

The development of specific psychological and pharmacological treatments to tackle first presentations of psychotic illnesses has been relatively slow. However, services to deliver existing evidence-based interventions to people at that early clinical stage have changed dramatically over the last 2 decades. Traditional multidisciplinary community mental health teams now work as specialized early intervention in psychosis teams. Seminal work, especially from Australia and the United Kingdom, has led to widespread adoption of these assertive treatment programs for young people in the initial phases of psychotic illnesses. In this context, rapid access and adherence to effective pharmacological treatments, specifically antipsychotics, play a fundamental role in “the shorter the DUP, the better the outcome” motto that early intervention in psychosis is predicated upon [1,2]. In fact, there is a plethora of evidence demonstrating that adherence to antipsychotic treatment has a positive impact on psychotic illness progression and longer-term outcomes such as hospital admissions, functioning, and suicide rates [3-5].

The introduction of early intervention programs has led clinicians toward a more accurate identification of the psychological and social interventions that each patient can benefit from; however, clinicians still face difficulties in selecting the antipsychotic medicine that better suits their patients [6-8]. Thus far, pragmatic randomized controlled trials have been the main source of scientific information to decide on the most effective and tolerable antipsychotics for patients with first-episode psychosis. These studies have found all-cause discontinuation rates for individual antipsychotics of approximately 40% or above during the first year of follow-up, which increases to 80% after 3 years of treatment even in the context of traditional early intervention in psychosis services [7,8]. These results fall short in terms of shifting clinicians’ trial-and-error approach to prescribing antipsychotics in clinical practice, which often ends in changes from those that do not yield sufficient therapeutic response or cause adverse effects [4]. This is further complicated by the fact that patients’ early experiences of antipsychotics nurture long-term perceptions of them; therefore, experiencing side effects or a lack of efficacy can make young individuals develop negative attitudes toward these drugs [9]. In fact, the high prevalence of adverse reactions in young, drug-naïve patients and lack of therapeutic response from antipsychotics are significant contributors to treatment discontinuation [9,10]. This stresses the need to tailor antipsychotic (and dose) selection to each patient from the very early stages of their psychotic illness.

While the use of pharmacogenetics (the effect of genetic factors on reactions to medicines) in people treated with antipsychotics has already found strong associations between treatment responses, side effects, and genetic variations, studies describing the clinical utility of pharmacogenetics are still very scarce and mainly limited to patients with severe and enduring psychotic disorders and poor response to treatment [11-13]. Notably, the systematic implementation of pharmacogenetics and its clinical effect on those experiencing the first episode of a psychotic illness has still not been tested. Personalized precision psychiatry using pharmacogenetics could help individualize antipsychotic treatment for patients with first-episode psychosis. It could reduce the time needed to find a tolerable and effective antipsychotic drug for people that were never exposed to such medications. Pharmacogenetics would simply be another tool that early intervention services could adopt and implement within their treatment pathways to improve medication adherence [13].

At the Salamanca University Healthcare Complex (CAUSA) in Spain, specifically in the Salamanca University Hospital (HUS), our unit of pharmacogenetics and precision medicine has been working on the application of pharmacogenetics to clinical practice for more than a decade [14]. We have developed an internationally pioneering method called 5-step precision medicine (5SPM) that addresses most of the implementation challenges outlined previously. The award-winning 5SPM model is based on updated scientific knowledge, integrating new technologies from up-to-date, highly efficient genotyping to state-of-the-art bioinformatics and artificial intelligence [13-17]. In fact, the 5SPM model is paving the way for the implementation of pharmacogenetics across different clinical specialties. In contrast to other existing methodologies, which are mostly guided by laboratory genetic results, the 5SPM method also addresses the specific needs and characteristics of the patient whom it is applied to, taking into consideration clinical and epidemiological variables as well as any other factor, such as polypharmacy, that could affect treatment response. Operationally, it is structured in the following five steps: (1) collection of clinical, epidemiological, and treatment data, including current prescriptions, diagnosis, and treatment response; (2) study of pharmacological interactions based on drug-specific pharmacokinetic pathways by processing databases such as the Pharmacogenomics Knowledge Base, PubMed–National Center for Biotechnology Information, Charite’s SuperCYP-Transformer, and the Pharmacogene Variation Consortium; (3) pharmacogenetic analysis of the genes that code enzymes involved in drug-specific metabolism; (4) modification or introduction of pharmacotherapy according to the data obtained in the previous 3 steps; and (5) analysis of the treatment outputs and, depending on clinical evolution, reassessment if needed.

The 5SPM model relies on a multidisciplinary approach, implying that technical and clinical staff must work closely together, and strictly adheres to ethical requirements such as comprehensive informed consent. This method has already shown quantifiable positive impact on the quality of life of patients in different clinical fields, including psychiatry. Since its inception, more than 1000 patients have benefited from it, and it has also generated additional phamacogenetics knowledge [13,16,18]. This is corroborated by a significant scientific body of evidence supporting the effectiveness and cost-efficiency of this method in real-world settings when compared to treatment as usual. The 5SPM approach has been successfully implemented in diverse psychiatric populations, including individuals with chronic psychotic disorders, bipolar disorder, and complex multimorbid presentations involving polypharmacy [13-19]. Clinical protocols guided by the 5SPM approach integrate pharmacogenetic data—particularly cytochrome P450 (CYP450) genotyping—with a patient’s clinical, pharmacological, and biological history to optimize treatment selection. In patients with poor response to antipsychotics, this approach has identified high rates of gene-drug and drug-drug interactions, allowing for targeted therapeutic adjustments that significantly reduced polytherapy and daily dosages, thereby lowering the risk of adverse effects and enhancing adherence [13]. Moreover, in broader psychiatric cohorts, pre-emptive pharmacogenetic testing has shown utility in preventing affective switching in bipolar disorder and mitigating side effects associated with selective serotonin reuptake inhibitor treatment based on cytochrome P2D6 and P2C19 metabolizer status [18]. These interventions have not only improved clinical outcomes but also demonstrated economic value, with cost-benefit ratios exceeding 3:1 in some studies and consistent reductions in hospitalization and treatment costs across patient groups [19]. Collectively, these findings support the clinical scalability of the 5SPM approach and its potential to enhance safety, efficacy, and cost-efficiency in precision psychiatry.

### Objectives

We have fully integrated the 5SPM method into our recently launched Prevention and Early Intervention in Mental Health (PRINT) program and shall evaluate its impact. The PRINT program is a novel clinical service that aims to provide early, comprehensive care to adolescents and young adults experiencing first-episode psychosis in Salamanca. This is one of only a few services of this kind in Spain, where early intervention is still not widespread. Considering that there is still a marked heterogeneity in treatment engagement and response among patients with first-episode psychosis in early intervention services worldwide [20], the PRINT program is refreshing the early intervention model by optimizing pharmacological choices for such a clinical group following the 5SPM methodology. Thus, the Clinical Utility of Early Intervention Including the 5SPM Method in First-Episode Psychosis (CLUMP) project aims to explore whether an early intervention model of personalized precision psychiatry including pharmacogenetics improves adherence to antipsychotic medicines and, therefore, clinical and functional outcomes in young people experiencing the first episode of a psychotic illness.

We hypothesize that integrating the 5SPM method into PRINT will significantly improve adherence to antipsychotic treatment and, consequently, enhance both clinical and functional outcomes.

The CLUMP project’s objectives will be to (1) introduce an innovative early intervention model of personalized precision psychiatry including the 5SPM method for patients with first-episode psychosis; (2) ascertain whether such a model can reduce the elevated discontinuation rates of antipsychotic medications among this group within the first year of follow-up by clinical services; (3) assess the impact of the new model on pragmatic efficacy measures such as hospital admissions and functional outcomes such as return to work or education; (4) determine whether this innovation can bring cost benefits to the public health care system and the wider economy; and (5) establish a blueprint for implementing this precision medicine model, specifically pharmacogenetics, across early intervention in psychosis programs nationally and internationally.

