## Methods

### Study Design

To test our hypothesis and achieve our objectives, we shall compare adherence to the first prescribed antipsychotic medication and pragmatic clinical and functional outcomes between 2 cohorts of patients with first-episode psychosis. One cohort will comprise patients treated before the implementation of an early intervention in psychosis model of personalized precision psychiatry, including pharmacogenetics, and the other will comprise patients treated under this new model. In addition, we shall compare the pharmacogenetic profiles and possible phenocopies (variations of phenotypes produced environmentally, eg, due to polypharmacy, rather than genetically) between these patients with first-episode psychosis and a national sample of patients with longer-term psychotic disorders or other mental health conditions to evaluate potential implications for clinical management at different stages of a psychotic illness and across mental disorders.

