### Clinical Management and Pharmacogenetics Analysis

Patients in cohort 1 will receive the recently introduced PRINT program, an early intervention in psychosis model, including the 5SPM method based on pharmacogenetics developed by our unit of pharmacogenetics and precision medicine at the HUS. As mentioned previously, the 5SPM method includes five steps: (1) collection of clinical, epidemiological, and treatment data; (2) study of pharmacological interactions based on drug-specific pharmacokinetic pathways; (3) pharmacogenetic analysis of the genes that code enzymes involved in drug-specific metabolism; (4) introduction of or change in pharmacotherapy according to the data obtained in the previous 3 steps; and (5) analysis of the treatment outputs and reassessment if needed. These steps will be preceded by an informed consent process. This preliminary procedure plus steps 1 to 4 will be conducted as soon as possible, ideally when a patient with a first episode of psychosis is identified by clinical services, aiming to minimize the time between the initial presentation and pharmacogenetics-informed decisions on pharmacotherapy. Step 5 (treatment review) will be carried out 6 months after antipsychotic treatment initiation. All steps will require a multidisciplinary approach and a shared decision-making process including patients or their family or legal representatives, especially if the patient lacks the mental capacity to make such decisions.

For the pharmacogenetics analysis (step 3), we shall use mass spectrometry and real-time polymerase chain reaction to study the genes encoding enzymes 1A2, 2B6, 2C9, 2C19, 2D6, 3A4, and 3A5 of the CYP450 family, in addition to transporter ABCB1. The CYP450 superfamily contains highly polymorphic genes. The usual approach to the relationship between genotypic variability and the metabolism of CYP450 substrates is based on the definition of metabolic phenotypes with their characteristic pharmacokinetic implications according to different genetic mechanisms. Metabolic profiles will be considered to make decisions on antipsychotic treatment choices. We already have enough technical support and pharmacogenetics evidence for most antipsychotics used in the early stages of a psychotic illness (ie, olanzapine, risperidone, paliperidone, quetiapine, aripiprazole, amisulpride, lurasidone, cariprazine, haloperidol, and zuclopenthixol).

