Cohort 2 will have received standard care provided by mental health services before the PRINT program implementation, specifically by mental health professionals working in generic community mental health teams that offer assessment and treatment to people who reside in their geographical catchment areas and experience a wide range of mental disorders, not only psychotic disorders.

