### Effect and Sample Size

We conducted a power calculation for the main outcome: the proportion of patients with first-episode psychosis who, by their treating clinician’s or their own decision, discontinue, for any reason, the first prescribed antipsychotic medication within 1 year. As stated previously, recent research studies, mostly carried out in early intervention settings, concur that 40% of patients with first-episode psychosis experience first prescribed antipsychotic drug discontinuation during the first year following treatment initiation [7,8]. This proportion may be even higher in patients receiving mainstream psychiatric care, such as our cohort 2. Considering the expectations behind the use of personalized precision medicine, PRINT should aim to reduce discontinuation rates to 10%. Therefore, for a power of 80% with (1) a significance level of .05 (2-sided), (2) all-cause discontinuation rate in cohort 1 (intervention) of 0.4, (3) all-cause discontinuation rate in cohort 2 (treatment as usual) of 0.1, and (4) an expected dropout or loss to follow-up rate of 0.2, our calculations would require a sample size of at least 38 patients in each cohort. We used the R statistical software *pwr* package for this calculation (version 4.4.2 for Windows; R Foundation for Statistical Computing).

In CAUSA, we have found an administrative incidence of 50 new patients aged 12 to 35 years every year. Thus, we would expect at least 75 patients eligible to be recruited for cohort 1 over 18 months. Using a conservative approach, if 25 patients (approximately 35%) do not agree to take part, we would still enroll 50 patients. This would be in addition to another 50 patients in our retrospective cohort 2 and pharmacogenetic data currently available at CAUSA from 100 patients with psychotic disorders of more than 5 years of evolution and another 100 patients with other mental disorders that we shall use for further comparative purposes, as outlined previously. This all accounts for a total of 300 participants contributing to this project.

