Therefore, the problem that we strive to solve is cultural, linked to prevailing trial-and-error prescribing of antipsychotics in clinical practice, as well as structural, concerning the evidence-policy-practice gap for tailoring drug treatments to patients with psychotic disorders at the earliest opportunity. Nonetheless, our new joint venture of early intervention in psychosis and applied precision medicine, combined with our previous experience using the 5SPM method for patients with mental disorders, should give us scientific and logistic traction to achieve our aims. Indeed, a guided implementation of pharmacogenetics for real-world clinical settings following the 5SPM methodology could help overcome patients’ and clinicians’ uncertainties and facilitate the use of this evidence-based innovation not only to address poor response to or adverse events from psychiatric medications in patients with established psychotic disorders but also to promote personalized and pre-emptive drug prescription [11]. The CLUMP project should be able to provide the first clear blueprint for implementing and evaluating the impact of personalized precision psychiatry based on pharmacogenetics in the context of early intervention programs for the benefit of young people experiencing the first episode of a severe mental illness such as schizophrenia.

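### The hypothesis and objective 5 credit 5SPM, but the only outcome comparison is PRINT including 5SPM against generic care, so it can support the package and cannot isolate 5SPM

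*Protocol article*

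**What the plan says.** Two levels of claim stand side by side in the protocol article.

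**Package level.** Under Objectives, the project "aims to explore whether an early intervention model of personalized precision psychiatry including pharmacogenetics improves adherence to antipsychotic medicines". Objectives 2 and 3 likewise ask what the model as a whole does to discontinuation, admissions and functional outcomes.

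**Component level.** The hypothesis, in the same section, reads "We hypothesize that integrating the 5SPM method into PRINT will significantly improve adherence to antipsychotic treatment". Objective 5 is to "establish a blueprint for implementing this precision medicine model, specifically pharmacogenetics, across early intervention in psychosis programs nationally and internationally". The closing text of Expected Findings, like the abstract's Conclusions, speaks of "evaluating the impact of personalized precision psychiatry based on pharmacogenetics".

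**The comparison.** Study Design ties the hypothesis to a two-cohort contrast: "To test our hypothesis and achieve our objectives, we shall compare adherence to the first prescribed antipsychotic medication", with one cohort treated before the new model and one under it. Clinical Management and Pharmacogenetics Analysis sets out what each cohort gets. For the prospective one: "Patients in cohort 1 will receive the recently introduced PRINT program, an early intervention in psychosis model, including the 5SPM method". Cohort 2 had standard care before PRINT existed, from "mental health professionals working in generic community mental health teams that offer assessment and treatment" for a wide range of disorders.

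**The planning rate.** Effect and Sample Size takes 40% one-year discontinuation from studies done mostly in early intervention settings, then adds: "This proportion may be even higher in patients receiving mainstream psychiatric care, such as our cohort 2".

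**Limitations** names the single centre and a possible status quo bias. It does not mention that the service model and 5SPM arrive together.

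**The concern.** Read as written, the hypothesis is about an increment: what 5SPM adds to PRINT. Testing that needs patients treated in PRINT without 5SPM, and there are none. Cohort 1 has both the specialised early intervention service and 5SPM; cohort 2 has neither. Any difference in discontinuation is the joint effect of the two, and the data cannot divide it.

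This matters most for the audience of objective 5. Early intervention programmes elsewhere already provide the service component. What they would want to know is the gain from adding 5SPM to it, and that is the quantity the comparison does not estimate. A significant primary result reported under the present hypothesis would invite them to credit pharmacogenetics with an effect that the service change alone could have produced.

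**Working it through.** **Step 1: what each group receives.**

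| Group | Early intervention service | 5SPM | Used for discontinuation comparison |
|---|---|---|---|
| Cohort 1 (50 planned) | yes | yes | yes |
| Cohort 2 (50 planned) | no | no | yes |
| Long-term psychosis (100) and other disorders (100) | not a first-episode PRINT comparison | not applicable | no; pharmacogenetic profiles and phenocopies |

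The row needed to isolate 5SPM (service yes, 5SPM no) is absent. Write the cohort difference in discontinuation risk as

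p(generic) − p(PRINT + 5SPM) = [p(generic) − p(PRINT alone)] + [p(PRINT alone) − p(PRINT + 5SPM)].

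The study estimates the left side. The hypothesis sentence concerns the second bracket. Because p(PRINT alone) is not observed, the two brackets cannot be separated.

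**Step 2: the plan's own sample size.** Inputs from Effect and Sample Size: 0.40 against 0.10, 80% power, two-sided 0.05, 20% dropout. With the arcsine effect size that the R pwr package uses:

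- h = 2·asin(√0.40) − 2·asin(√0.10) = 0.726
- n = 2·((1.960 + 0.842)/0.726)² = 29.8, rounded up to 30
- 30/(1 − 0.2) = 37.5, rounded up to 38

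The stated 38 per cohort reproduces and is not in dispute. The text attaches 0.4 to cohort 1 and 0.1 to cohort 2, the reverse of its own rationale; this does not change n. What matters here is that the 0.40 comes mostly from early intervention settings, while the actual comparator is generic care.

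**Step 3: how often the primary test is significant when 5SPM adds nothing.** Assumptions: 5SPM has no effect, PRINT runs at 0.40 (the cited figure), the cohorts differ in no other way, and generic care runs at an assumed rate p. The documents give no value for p, so a range is shown. The method is exact enumeration of two independent binomial counts X (generic) and Y (PRINT), summing P(X=x)·P(Y=y) over all tables where the uncorrected chi-square exceeds 3.841. The evaluable number after 20% loss is 50 × 0.8 = 40.

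| Assumed generic-care rate | 50 per cohort | 40 per cohort |
|---|---|---|
| 0.45 | 0.085 | 0.079 |
| 0.50 | 0.184 | 0.157 |
| 0.55 | 0.345 | 0.288 |
| 0.60 | 0.543 | 0.458 |
| 0.65 | 0.734 | 0.639 |

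Statistical Analysis does not say whether a continuity correction applies. With one, the values at 50 per cohort for 0.55, 0.60 and 0.65 fall to 0.27, 0.46 and 0.66. In every row the test is doing its job: it detects a real difference between services. The error would lie only in attributing that difference to 5SPM.

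**The case against.** The strongest reply is that the document is mostly worded for the package. The project name refers to early intervention including 5SPM, the aim and objectives 1 to 3 refer to the model, Study Design contrasts care before and under that model, and the 10% target is set for PRINT. Objectives also says that 5SPM is fully integrated into PRINT, so the hypothesis sentence could be meant as a description of the integrated programme. Most of this stands, and it limits the point to the hypothesis sentence, objective 5, the concluding text and the missing limitation. It does not remove the point: on its plain reading the hypothesis is about adding 5SPM, and objective 5 names pharmacogenetics specifically.

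A second reply is that the illustration depends on a generic-care rate nobody has stated. That also stands. The protocol says the rate may be higher, not that it is, and uses 0.40 for planning. At 0.45 the probability is only 0.085. In these scenarios cohort 1 would also sit near 40%, visibly far from the 10% target.

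A reader might infer that a positive result would be worthless, or that the primary test is invalid. The documents do not support that. The comparison bears directly on the package question that the aim asks, and this point leaves that test intact. Nor do they support saying that generic care does discontinue more.

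**Conclusion.** The point holds in a limited form. The hypothesis sentence and objective 5 go beyond what the two-cohort comparison can identify; the aim and objectives 2 and 3 do not. A significant result can count for PRINT including 5SPM against pre-PRINT generic care. It cannot show how much of the difference, if any, is due to 5SPM. This follows from the structure of the groups and needs no numerical assumption.

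The size of the possible misattribution does rest on assumptions. With 5SPM adding nothing and PRINT at 40%, the chance of a significant result runs from 0.085 to 0.734 with 50 per cohort as the assumed generic-care rate goes from 45% to 65%, and from 0.079 to 0.639 with 40 evaluable. If generic care also runs at 40%, there is no inflation from this source. The figures illustrate the risk and are not a forecast.

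**What to change.** - **Hypothesis:** restate it at package level, for example: *PRINT, an early intervention programme including 5SPM, reduces one-year all-cause discontinuation of the first antipsychotic compared with pre-PRINT standard care.*
- **Objective 5 and the conclusions in the abstract and Expected Findings:** describe the blueprint as one for the package, with pharmacogenetics as a component whose separate effect was not estimated.
- **Limitations:** add that 5SPM was introduced together with the new early intervention service and that its contribution cannot be separated from it.

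Two supplementary analyses may look attractive, but neither would repair the gap. Comparing cohort 1 with the 40% figure swaps one historical comparator for external studies, and Background gives that figure as approximate or above. Comparing genotyped cohort 2 patients by whether their first drug matched what 5SPM would have advised depends on optional consent to genotyping (see Participants). It also needs a retrospective 5SPM review that is not planned. Leave both out, or label them exploratory and unable to isolate 5SPM.

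The cost is rewording and a narrower headline claim. No new arm, extra patients or change to care is needed.
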